# Chinese herbal medicine *bi min fang* for allergic rhinitis: protocol for a double-blind, double-dummy, randomized controlled trial

**DOI:** 10.1186/s13063-018-3151-0

**Published:** 2019-01-18

**Keywords:** Allergic rhinitis, Chinese herbal medicine, Randomized controlled trial, Cytokines, Gut microbiota

## Abstract

**Background:**

People with allergic rhinitis (AR) often seek help from Chinese medicine due to dissatisfaction with conventional treatments. Lung-spleen *qi* deficiency syndrome (LSQDS) is the most common type of AR, and the Chinese herbal medicine formula *bi min fang* (BMF) is commonly prescribed for AR patients with LSQDS. However, direct evidence supporting its efficacy and safety is not available, and its potential mechanism of action remains unclear.

**Methods/design:**

This paper presents a double-blind, double-dummy, randomized controlled trial. After a 2-week run-in period, 80 AR patients with LSQDS will be recruited and randomly allocated to the BMF group or the control group in a 1:1 ratio. The patients in the BMF group will receive BMF and the placebo for levocetirizine hydrochloride orally, while the control group participants will receive levocetirizine hydrochloride and the placebo for BMF orally. All participants will receive 4 weeks of treatment and 12 weeks of follow-up.

The primary outcome is a change in the Total Nasal Symptom Score (TNSS). Secondary outcomes include changes in scores for the standard version of the Rhinoconjunctivitis Quality of Life Questionnaire (RQLQ(S)), and visual analog scale (VAS); changes in serum levels of the cytokines interleukin-4, interferon-γ, transforming growth factor β-1, and interleukin-17; and changes in the gut microbiota composition in the stool. The TNSS, RQLQ(S), and VAS will be recorded at the beginning of, middle of and after the treatment period and at the end of each month in the 3-month follow-up period. Blood and stool samples will be collected at baseline and the end of the treatment. The aforementioned four cytokines will be detected in the serum using enzyme-linked immunosorbent assays, and the stool gut microbiota will be detected using 16S ribosomal ribonucleic acid sequencing. Any side effects of the treatment will be recorded.

**Discussion:**

The results of this trial will provide consolidated evidence of the effect of BMF on AR and the potential mechanism by which BMF acts. This study will be the first to explore the mechanism of action of Chinese herbal medicine on the gut microbiota in AR.

**Trial registration:**

Chinese Clinical Trial Registry, ChiCTR-IPR-17010970. Registered on 23 March 2017.

**Electronic supplementary material:**

The online version of this article (10.1186/s13063-018-3151-0) contains supplementary material, which is available to authorized users.

## Background

Allergic rhinitis (AR) is a symptomatic nasal disorder caused by an immunoglobulin E (IgE)-mediated immunological reaction to allergen exposure [1] and is a global health problem that affects people of all ages. The worldwide incidence of AR is 10–20% [2], and the prevalence of self-reported AR in China is 11.1–19.1% [3, 4]. Classic symptoms of AR include rhinorrhea, nasal obstruction, nasal itching, and sneezing [1], and the disorder is classified as intermittent AR or persistent AR based on the duration of symptoms [1]. AR can lead to sleep cycle disorders, emotional imbalance, impaired ability to perform normal daily activities, severely decreased quality of life, and significant economic burden [1, 5]. Moreover, AR also serves as a trigger for other diseases, such as bronchial asthma [1]. Current conventional management of AR primarily includes allergen avoidance, pharmacotherapy, immunotherapy, and patient education [1, 6]. Second-generation H1 antihistamines, nasal glucocorticosteroids and leukotriene antagonists are recommended as the first-line therapy [1, 2, 6]. However, due to unsatisfactory results with conventional treatment, AR patients are increasingly seeking complementary and alternative therapies [7].

Chinese herbal medicine (CHM) is a well-tolerated choice for AR patients seeking complementary and alternative therapies to reduce AR symptoms [7]. The latest Chinese guidelines for the diagnosis and treatment of allergic rhinitis (2015, Tianjin) suggest that CHM can be applied as an auxiliary method of treating AR [4]. CHM is an important type of complementary alternative medicine, and several studies have focused on the use of CHM to treat AR. A double-blind randomized controlled trial (RCT) with a design incorporating repeated measures and three parallel groups showed that CHM is useful for ameliorating symptoms, enhancing quality of life, and strengthening body constitution in patients with AR, and all participants in this study were subjected to syndrome differentiation [8]. Another two RCTs showed that CHM safely reduces the nasal symptoms of AR, although the participants in those studies were included without syndrome differentiation [9, 10]. One systematic review and meta-analysis of seven RCTs comparing oral CHM to a placebo showed that CHM was able to reduce total nasal symptom scores. However, details of the CHM formulas used in the studies included were not investigated, and the syndromes of the participants were not described. Furthermore, the sample sizes of the RCTs were small, and all the trials had certain methodological limitations. Thus, the authors could not draw a firm conclusion regarding the effects of CHM on AR [11]. Overall, CHM appears to be a promising intervention for patients with AR, and more rigorous RCTs with large sample sizes are needed to further define its effectiveness.

Syndrome differentiation or pattern identification is the core treatment principle of traditional Chinese medicine (TCM), and an accurate treatment for an AR patient must be prescribed according to their body constitution. Based on our clinical observations, a considerable number of AR sufferers are diagnosed with lung and spleen *qi* deficiency syndrome (LSQDS), and this observation is supported by the results of published studies [12–16]. Therefore, according to TCM theory, tonifying lung and spleen *qi* is the treatment principle for AR patients with LSQDS.

Two classic CHM formulas, *bu zhong yi qi tang* and *yu ping feng san*, are commonly used for allergic diseases [17]. In our clinical practice, *bi min fang* (BMF), which is composed of modified *bu zhong yi qi tang* and *yu ping feng san*, is the most commonly used CHM formula for AR patients with LSQDS. The composition of BMF is based on a systematic review of classic reference books, articles obtained from the PubMed database [8, 17], the Chinese scientific literature, clinical guidelines [18], and our clinical experience [19].

Existing evidence supports the beneficial effects of two original TCM formulas on AR [8, 20–22]. Clinical studies have shown that *yu ping feng san* can improve symptoms [8, 21] and quality of life [8] and decrease the levels of interleukin-4 (IL-4) and IgE in AR patients [21]. Indeed, a glucosidic extract from *yu ping feng san* reportedly exerts anti-inflammatory and immunoregulatory effects by inducing activation of T helper cells and regulating other subsets of T lymphocytes [22]. *Bu zhong yi qi tang* was also found to reduce AR symptoms, with suppressive effects on the total serum level of IgE and IL-4-stimulated production of prostaglandin E2, leukotriene C4, and COX-2 mRNA expression in IL-4-stimulated polymorphonuclear neutrophils [20]. Thus, it is reasonable to hypothesize that BMF is effective for the treatment of AR.

Most CHM is administered orally, whereby formulations are ingested, transferred, digested, and absorbed through the gastrointestinal system. Accordingly, CHM may influence the gastrointestinal system, including the intestinal mucosa and gut microbiota, the latter of which is essential for health and closely linked to diseases [23]. For instance, several studies have demonstrated that low gut microbiota diversity is associated with a high risk of allergic diseases [24–28]. Other studies have reported that the characteristics of seasonal AR include a lower diversity of intestinal *Bifidobacterium* [29], with a reduction of *Bifidobacterium*, *Clostridium*, and *Bacteroides* [30] and increased populations of *Bacteroides fragilis* [31]. A few systematic reviews and studies indicate that certain probiotics are beneficial for patients with AR [32–35]. We hypothesize that components of CHM, such as glycosides and oligosaccharides [36], may influence the gut microbiota in the same manner as an oral probiotic by regulating local intestinal immunological conditions and thereby, achieving systematic immunomodulation [37, 38].

Placeboes have been widely used in the control groups of previous clinical studies of AR treated with pharmacotherapy and immunotherapy, with the placebo control treatment resulting in over 50% symptom relief [6]. Therefore, in this study, we selected Western medicine as the positive control instead of a placebo. Levocetirizine, a second-generation antihistamine that acts on peripheral histamine H1 receptors, has a strong anti-allergic effect without a sedative effect, and it is used for relieving and preventing not only AR symptoms but also those of other allergic diseases. After careful consideration of the adverse effects and the desired effect, we chose levocetirizine as the intervention for the control group.

To blind the participants and the researchers adequately, a placebo for the intervention given to the other group will be administered to both groups. We designed a double-blind, double-dummy RCT for AR patients with LSQDS. The objectives are to assess the efficacy of BMF for AR patients with LSQDS and to explore the mechanism of BMF in treating AR with respect to the immune response and gut microbiota.

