### Sample size calculation

This study is mainly focused on determining the efficacy of BMF for AR patients with LSQDS. The primary outcome is the TNSS. With reference to data from a previous study [46] and our clinical observations, the sample size was calculated using the noninferiority test for two means with software PASS 2011. We assumed that the TNSS of the treatment group will be 5.53 ± 2.79 and that of the control group will be 6.64 ± 3.06. To obtain a significance level of 5%, a power of 90%, and a noninferiority margin of 0.92, 74 participants are required. Allowing for an 8% dropout rate, 80 participants are needed, with 40 in each group.

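### The placebo response is cited as the reason to omit placebo, yet a noninferior result against levocetirizine cannot by itself support the unqualified efficacy claim

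*Protocol article*

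**What the plan says.** The Background of the protocol article refers to placebo-controlled trials of drug treatment and immunotherapy and explains from them why no placebo arm is used: "with the placebo control treatment resulting in over 50% symptom relief [6]. Therefore, in this study, we selected Western medicine as the positive control instead". It calls levocetirizine strongly anti-allergic but gives no figure for its effect over placebo. The same section sets the aim: "The objectives are to assess the efficacy of BMF for AR patients with LSQDS", together with an exploration of mechanism. Neither the comparator nor noninferiority appears in that objective.

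Under Sample size calculation, the text opens by saying that the study is mainly about the efficacy of BMF. It then reports that "the sample size was calculated using the noninferiority test for two means with software PASS 2011". The inputs are: "We assumed that the TNSS of the treatment group will be 5.53 ± 2.79 and that of the control group will be 6.64 ± 3.06". The result is: "To obtain a significance level of 5%, a power of 90%, and a noninferiority margin of 0.92, 74 participants are required". The margin is not derived.

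The Discussion part of the Abstract promises: "The results of this trial will provide consolidated evidence of the effect of BMF on AR". The main Discussion lists three limitations, and the lack of a placebo arm is not among them. Both arms receive placebo only as the double dummy, so no participant receives placebo alone.

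**The concern.** A noninferiority result says that the new treatment is not worse than the comparator by more than the margin. It becomes evidence that the new treatment works only if the comparator is known to beat placebo by more than that margin under similar conditions. When placebo patients improve a great deal, two arms can look alike because both show placebo response and natural fluctuation. A large placebo response is therefore a reason to keep a placebo arm, or to tie the margin to a documented effect of the active control. It is not a reason to do without both.

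What is at stake is the main conclusion. The Background of the Abstract says that direct evidence of BMF's efficacy is not available, so this trial is meant to supply it. If noninferiority is met and the conclusion follows the stated objective, efficacy could be claimed from a result that does not establish it.

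**Working it through.** **1. Reproduce the sample size.** Inputs from Sample size calculation: means 5.53 (BMF) and 6.64 (control), SDs 2.79 and 3.06, margin 0.92, power 90%, significance level 5% (sidedness not stated).

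- Pooled SD = √[(2.79² + 3.06²)/2] = 2.928.
- Assumed difference = 5.53 − 6.64 = −1.11, in favour of BMF because lower scores are better.
- Normal formula, one-sided 5%: n per arm = 2 × 2.928² × (1.645 + 1.282)² / (0.92 + 1.11)² ≈ 35.6, so 36 per arm (72 in total).
- The same calculation with the noncentral t distribution gives 37 per arm, **74 in total**, as stated.
- One-sided 2.5% gives 88 (normal) or 90 (t), which does not match.

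If the two means were reductions, with higher better, BMF would be 1.11 worse. That lies outside the 0.92 margin, so no sample size would exist. The means are therefore scores under treatment, and the trial is powered for noninferiority with an assumed BMF advantage.

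**2. What a noninferiority pass requires.** With 37 per arm, the standard error is 2.928 × √(2/37) = 0.681 and the one-sided 5% half-width is 1.13. A pass needs an observed difference below 0.92 − 1.13 = −0.21, so the observed BMF mean must be about 0.21 points better than control (about 6.43 or lower if control is 6.64).

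**3. Power for superiority over levocetirizine, the route that would be informative without placebo.** At a true difference of 1.11, two-sided 5%, normal approximation:

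- 37 per arm: 1.11/0.681 = 1.63; 1.63 − 1.96 = −0.33; power about **37%**.
- 40 per arm: power about **40%**.
- A one-sided 5% test with 37 per arm gives about 49%.

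Even if the planning assumptions are exactly right, the more likely outcome is noninferiority without superiority at two-sided 5%.

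**4. Illustration only: the quoted placebo response against the planned means.** Assumption: the relief of over 50% is a mean score reduction on a scale comparable to TNSS. Outcome measurement defines TNSS as four symptoms scored 0 to 3, so the maximum is 4 × 3 = 12. No baseline TNSS is given, so a range is shown.

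| Assumed mean baseline | Control relief, 1 − 6.64/baseline | BMF relief, 1 − 5.53/baseline |
|---|---|---|
| 12 (ceiling) | 44.7% | 53.9% |
| 10 | 33.6% | 44.7% |
| 8 | 17.0% | 30.9% |

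For the control arm to reach 50% relief, baseline would have to be 2 × 6.64 = 13.28, which is off the scale. The assumed BMF mean exceeds 50% only if mean baseline is above 2 × 5.53 = 11.06. If the quoted figure is instead the proportion of patients relieved, this comparison does not apply. Steps 1 to 3 are unaffected.

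**The case against.** An active-control design is legitimate in itself, and the article states openly that it used a noninferiority calculation. Nothing in it says that noninferiority will be reported as proof of an effect over placebo. Efficacy relative to levocetirizine can be estimated, and superiority would be informative. These points stand, and they limit the fault to the stated rationale and the unqualified claim.

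A reader might go further and infer that, on the article's own figures, a noninferior BMF need be no better than placebo, because 6.64 on a 12-point scale is at most 44.7% relief. The document does not support that as a finding. The placebo figure comes from an outside source, across drug and immunotherapy trials, with no scale, duration or population. It may be a responder proportion. The TNSS means come from a different previous study and clinical observations. An implied control relief of 34% at an assumed baseline of 10 may as easily signal mismatched measures as an ineffective control.

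A reader might also picture BMF passing at 6.64 + 0.92 = 7.56. An observed mean of 7.56 against 6.64 would fail, since a pass needs BMF to be observed about 0.21 points better. If the true mean were 7.56, the trial would pass only about 5% of the time.

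**Conclusion.** The point holds as one of rationale and permitted conclusion. The reason given for dropping placebo runs the wrong way, the 0.92 margin has no stated link to a levocetirizine-placebo effect, and the objective and Abstract promise efficacy without qualification. Noninferiority alone would be compatible with placebo response in both arms.

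It would be too strong to say that the trial cannot deliver evidence of efficacy. Superiority over levocetirizine would be informative, although power for it is only about 37% to 40% at the assumed 1.11-point difference and two-sided 5%. That figure rests on the article's own means and SDs, read as scores under treatment, which is the reading that reproduces 74. The 44.7% ceiling is an illustration conditional on how the placebo figure is defined, and the verdict does not depend on it. This should be fixed. It leaves the sample size and the planned comparison unchanged.

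**What to change.** No new arm is proposed; Trial status reports 76 patients already recruited.

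1. Restate the primary objective and permitted conclusion: success shows that BMF is noninferior to levocetirizine within 0.92 TNSS points. Do not claim efficacy of BMF in itself from noninferiority alone, unless the margin is justified against a documented levocetirizine-placebo effect or BMF is shown superior to levocetirizine. Align the Abstract, the Background objective and the opening of Sample size calculation with this.
2. Correct the rationale in the Background, so that the placebo response is no longer given as a reason to omit placebo, and add the lack of a placebo arm to the limitations in the Discussion.
3. Report the change in TNSS from baseline in each arm with its confidence interval, as description only. Do not attach a rule that the control arm must exceed 50%. That would set an uncontrolled within-arm change against an undefined historical figure, and a control mean of 6.64 would fail it even with baseline at 12.

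The cost is a few sentences and one descriptive summary. The downside is a more modest claim.

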## Methods/design

### Study design and setting

This is a double-blind, double-dummy RCT. In total, 80 participants will be recruited from the Guangdong Provincial Hospital of Chinese Medicine (GDPHCM), Guangzhou, China. The flow chart and study period are shown in Figs. 1 and 2, respectively. After obtaining written informed consent, a 2-week run-in period will be implemented, and then eligible participants will be randomly assigned to a CHM group or a control group in a 1:1 ratio. Because anther study designed to identify differences in the gut microbiota between AR patients and healthy controls will utilize stool samples from the same group of AR participants, additional consent provisions for collection and use of these participants’ data and stool samples will be explained to the participants.

**Fig. 1 Fig1:**
[figure not shown]
Trial flow chart

**Fig. 2 Fig2:**
[figure not shown]
Study period

### Participants

Participants will be recruited via a local advertisement and doctor referrals from otorhinolaryngology clinics at GDPHCM. Information about the study, processing, and scheduling will be carefully explained before enrollment. Participants must meet the Western medicine diagnostic criteria for AR (Table 1) [4] and the TCM syndrome diagnostic criteria for LSQDS (Table 2). Syndrome differentiation will be determined by two independent qualified TCM otolaryngologists. Participants can complete their case report forms (CRFs) independently, and blood and stool samples can be collected according to the instructions.

**Table 1 Tab1:** Western medicine diagnostic criteria for allergic rhinitis

Symptoms	Two or more symptoms such as rhinorrhea, nasal obstruction, nasal itching, and sneezing, persisting for a cumulative period greater than 1 h per day. These symptoms may be accompanied by itchy and red eyes and tears.
Signs	The nasal mucosa is pale and edematous. Nasal secretions are watery.
Allergen test	At least one type of skin prick test or serum-specific IgE test is positive.

**Table 2 Tab2:** Diagnostic criteria for TCM differentiation of lung and spleen *qi* deficiency syndrome

History	Participants may have a personal or family history of allergies.
Clinical symptoms	The clinical symptoms are characteristically sudden and repeated. The main symptoms of AR are nasal itching, paroxysmal sneezing, watery rhinorrhea, and nasal congestion. These symptoms may be accompanied by itchiness of the eyes, pharynx, or soft palate.
Signs	The nasal mucosa is pale gray, pale blue, or red. The nasal turbinate is congested, and the nasal cavity is filled with a watery discharge. All these signs are unapparent when in remission. A light pink tongue body with a thin white coating or teeth marks on the sides and a thin and weak pulse are also characteristic.
Other laboratory tests	Immunological tests such as a skin prick test and serum IgE test are helpful in making a diagnosis.

*AR* allergic rhinitis, *TCM* traditional Chinese medicine

### Eligibility criteria

Inclusion criteria:In accordance with the Western medicine diagnostic criteria for AR. Presence of persistent AR and meeting the criteria for lung and spleen *qi* deficiency in TCMAge 18 to 65 years old, with no sex limitationHas not taken hormones or antibiotics in the preceding 3 months and has not consumed yogurt or prebiotics for 1 month preceding the trialParticipants provided informed written consent and volunteered to participate in the study.Participants can complete the case report forms (CRFs) independently, and blood and stool samples can be collected according to the instructions.

Exclusion criteria:Patients with similar nasal diseases such as acute rhinitis, vasomotor rhinitis, autonomic nervous rhinitis, eosinophilia nonallergic rhinitis, and allergic sinusitisPregnant women. The trial will be suspended if a participant becomes pregnantParticipants who cannot fully cooperate with the trial due to mental or behavioral disordersParticipants who frequently change their work place, resulting in difficulty with follow-upParticipants who drive or work high above the ground

### Randomization and allocation concealment

Randomization will be performed by the Key Unit of Methodology in Clinical Research of GDPHCM. The PROCPLAN process statements of the SAS statistics and analysis system (SAS Institute Inc., Cary, NC, USA) will be used to generate random numbers, which will then be enclosed in opaque envelopes. Attention will be paid to the concealment of the randomization. Eligible participants will be randomly assigned to either the BMF group or the control group.

Treatment allocation will be concealed and held by one member of the research team. To ensure adequate concealment, the participants will be given sequential treatment cards by independent researchers. The participants will receive an opaque envelope and allocated to one of the two groups according to the serial number and group name printed on their treatment card.

